### Ancillary outcome measures

#### Change in family caregiver resourcefulness

Resourcefulness is measured using the 28-item Caregiver Resourcefulness Scale (*α* = 0.85) [42]. This scale has two factors: (1) help-seeking and (2) self-help. Caregivers are asked the frequency with which they use different strategies to manage challenges and may respond: not at all like me (0), pretty much not like me (1), a little bit not like me (2), a little bit like me (3), pretty much like much like me (4), or very much like me (5). Items are added together to create a total score. Scores range from 0 to 140, where higher scores indicate higher levels of resourcefulness.

#### Change in quality of care by caregiver

Quality of caregiving according to the caregiver will be measured with the Task Management Strategy Index (TMSI; *α* = 0.74 to 0.81) [43]. The 19-item TMSI was developed to assess caregivers’ ability to manage their family member’s functional disabilities [44]. Caregivers are asked how often they engage in strategies that support quality care. Caregivers indicate never (1), rarely (2), sometimes (3), often (4), or always (5). Scores range from 19 to 95. Higher scores indicate higher quality of caregiving.

### Participant timeline {13}

Participants will complete a baseline survey up to 3 weeks before randomization. Once randomized, they will participate in either the intervention or control group condition once weekly for 6 weeks. A follow-up survey will be completed within 3 weeks post-intervention. A third and fourth follow-up survey will be administered 3 and 6 months post-intervention. Once the participant completes all study activities, they will receive the workbook materials for whichever program into which they were not randomly allocated to participate. Figure 1 illustrates this timeline.

**Fig. 1 Fig1:**
[figure not shown]
Timeline of study events for participants

### Recruitment {15}

Recruitment will occur nationally from multiple sources. To enroll *N* = 200 caregivers, the investigators will partner with a consulting firm specializing in Alzheimer’s disease research. This organization will develop a marketing strategy for materials such as flyers, in addition to their own proprietary in-person and online direct recruitment approaches. Researchers are also partnering with community-based organizations to share information via newsletters and existing social media accounts, such as through the California Caregiver Resource Centers (https://www.caregivercalifornia.org/). Researchers will also connect with direct service providers at these organizations to encourage them to share information with family caregivers with whom they work and provide a “warm hand off” to the study team [45]. Prior to enrolment, study team members will participate in a training informed by the *Network, Give first, Advocate for research, Give back, Evaluate, and Design and Develop* Model developed at the Rush University Alzheimer’s Disease Research Center [46–48]. This training will include a focus on recruiting caregivers who are severely underrepresented in current AD/ADRD research, including African American and Hispanic caregivers, as findings from the REACH II trial indicate culturally sensitive training may improve sample representativeness [49]. The recruitment approaches applied in this study will be dynamic. Ongoing monitoring of recruitment approaches, such as assessing enrolment following the use of a novel recruitment approach, will guide recruitment decisions. The researchers will recruit up to 16 cohorts of 12 to 24 caregivers each, such that randomized cohorts will be assigned to a group of at least *n* = 6 participants, but no groups will be larger than *n* = 12.

## Assignment of interventions: allocation

### Sequence generation {16a}

We will use stratified block randomization to assign participants to the intervention or control group at a 1:1 ratio. Consented participants will be randomized in variable block sizes once participants complete the baseline survey. Further, the study team will use stratification by race and ethnicity to prevent an unbalanced distribution of Hispanic and African Americans between the intervention and control conditions.

### Concealment mechanism {16b}

The randomization list will be generated in Stata 18 before the beginning of the trial. Only the PI and project manager can access the sequence file and REDCap project where randomization occurs. Block sizes will be known to the PI and project manager. Sequential randomization of cases as baseline surveys are completed, limited access to this schema, and pre-upload of the sequencing schema support concealment.

## Assignment of interventions: blinding

### Who will be blinded {17a}

The study statistician, data analyst, and research assistants who are involved in post-randomization data collection will be blinded to the intervention assignment. Participants, the PI, and the project manager will not be blinded. To maintain blinding, the statistician and data analyst will receive de-identified data on which to run analyses, wherein allocation will be indicated using a binomial variable not defined in the study codebook. Data collectors will receive participant contact information from the project manager when survey collection is scheduled but will not be told about participant allocation. Participants will be informed that the data collector is unaware of which program they completed at the beginning of the call.

### Procedure for unblinding if needed {17b}

The design of this study is open label with only outcome assessors, the statistician and data analysts being blinded so unblinding will not occur.

## Data collection and management

### Plans for assessment and collection of outcomes {18a}

Research assistants will enter research data directly into REDCap while completing Zoom-administered surveys [50]. REDCap is a secure, HIPAA-compliant survey data collection platform. Research assistants will share slide decks with questions and response options listed as each item is asked to promote focus and remind participants of response options. All data collectors will complete training, which includes practicing administering at least one recorded practice survey.

### Plans to promote participant retention and complete follow-up {18b}

To support retention, caregivers will receive a welcome packet in the mail with their participant workbook. This welcome packet will include a letter from the investigator team thanking participants for their time and reminding them of the importance of trial participation. Participants will also receive a branded writing utensil and fridge magnet to remind them of their study participation with a message that reinforces the importance of their contribution. Prior research has found that similar motivational approaches can promote participant retention [51]. In addition, following best practices from prior trials to the extent that it is feasible, participants will work with consistent study staff and will have multiple options to schedule interview times [52, 53].

### Data management {19}

To check the accuracy of data entry, the project manager or PI will select 5% of surveys due for data collection for each cohort. Data quality checks will consist of video recording Zoom survey data collection and having a second study team member mark the accuracy of how response options were captured in a REDCap form. The program manager or PI will notify data collectors if their Zoom survey was selected for a quality check and will review data entry quality check reports monthly. If reports indicate a rate of data entry error at 5% or higher on any single survey, the person conducting data entry will undergo retraining. If this occurs a second time, the data collector will be removed from the study to prevent inaccurate data entry from affecting results.

### Confidentiality {27}

To preserve participant confidentiality, during the trial, participants identifying information will be stored in a separate REDCap folder from their outcome data. Each study participant will be identified using two unique IDs: a sequentially generated identifier used to track participant status in the trial and a second four-digit identifier generated using a random number sequence to label all study data. A study key to connect identifiable information to study data will be stored in an encrypted folder available only to the PI and project manager. When data collectors are assigned to collect follow-up survey data, they will be provided with the participant’s name, phone number, and a link to the designated study survey. All participant identifying information will be deleted at the end of the trial after a summary of study results is shared with participants.

### Plans for collection, laboratory evaluation, and storage of biological specimens for genetic or molecular analysis in this trial/future use {33}

Not applicable. The research team is not collecting biological specimens as a part of this study.

## Statistical methods

### Statistical methods for primary and secondary outcomes {20a}

#### Preliminary descriptive analyses

Prior to running models to test study hypotheses, the investigators will calculate means/standard deviations on continuous variables and frequencies/percentages for categorical variables for each survey (e.g., baseline) for both the intervention and control group participants. Analyses of primary and secondary outcomes will be stratified by race, ethnicity, and gender. We will visually analyze box-and-whisker plots to detect potential outliers.

#### Bivariate analyses

Next, three sets of paired *t*-test analyses will be conducted using primary and secondary outcome scores from baseline to the (1) post-intervention, (2) 3-month survey, and (3) 6-month survey for both the *LST* and active control group. We anticipate that *LST* participants will demonstrate statistically significant differences in mean self-efficacy and secondary outcomes for each *t*-test but that there will not be a significant difference between means for the active control group. We will also visually analyze spaghetti plots that chart each outcome variable.

#### Selecting covariates

Before running models to test study hypotheses, the investigators will conduct additional bivariate tests (e.g., Pearson chi-squared) to compare the characteristics of participants randomized into the intervention and active control groups to confirm that groups are balanced in terms of sample characteristics and possible confounders. Variables that demonstrate statistically significant differences in means or distribution at *α* = 0.10 between study arms will be included as model covariates. Important covariates such as age, gender, race, and ethnicity will be included in models, regardless of their balance between two groups.

#### Direct effects of the Learning Skills Together intervention

To test for intervention effects of *LST* compared to the control condition, we will apply generalized estimating equation (GEE) models with an identity link and an unstructured correlation matrix to data. The models will include group assignment (intervention), time, and interaction between the group and time. A multivariate Wald test will be performed to see whether there is any group × time interaction. Once this joint test yields a significant result (*α* = 0.05), we will test if each regression coefficient of the group × time interaction demonstrates a *p*-value of < 0.05. If the model coefficient shows a positive association with self-efficacy, this will support our hypothesis that participation in *LST* improves caregiver self-efficacy relative to participation in an active control group. These analyses will be repeated for the outcomes measuring self-efficacy with complex care tasks, as well as secondary outcomes of depressive symptomology and negative appraisal of BPSD.

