## Objectives {7}

### Primary objective

The primary objective of this study is to determine whether participation in the *LST* intervention: (1) improves caregiver self-efficacy (primary outcome) overall and related to complex care for persons living with AD/ADRD and (2) reduces depressive symptomatology and negative appraisals of BPSD (secondary outcomes) relative to a structurally equivalent control condition among family caregivers to persons living with AD/ADRD. Further, the investigators will examine whether self-efficacy functions as a mediator of secondary outcomes. If a mediating effect is found, it would support the application of self-efficacy as an intervention mechanism.

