### Primary outcome measures

#### Overall family caregiver self-efficacy

The primary outcome measure in this trial will be the change in caregivers’ average scores on the 8-item Caregiver Self-Efficacy Scale from baseline until each follow-up survey [37]. This measure was selected because it provides a more concise measure of self-efficacy than prior, domain-specific scales and demonstrates reliability (*α* = 0.88 to 0.89). On a scale of 1 to 10, participants are asked to rate their confidence with 8 aspects of caregiving (e.g., controlling upsetting thoughts). Scores range from 8 to 80, with higher scores indicating higher caregiver self-efficacy levels.

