#### Family caregiver self-efficacy with complex care

There are no validated scales to measure caregiver self-efficacy specific to complex care. Thus, the authors generated a 16-item measure structured after the Caregiver Self-Efficacy Scale that asks caregivers to rate their confidence in handling various complex care tasks. This 16-item scale asks about how confident caregivers feel, from 0 (not at all confident) to 5 (very confident), with various complex care tasks (e.g., Managing incontinence issues) [28]. Pilot data showed high internal consistency (*α* = 0.89). Scores range from 0 to 80, with higher scores indicating higher caregiver self-efficacy levels with complex care.

While not measuring self-efficacy per se, the related construct of caregiver confidence with complex care will also be measured using the Caregiver Confidence in Sign/Symptom Management Scale (*α* = 0.91), which subscales for Knowledge of Symptoms (*α* = 0.56), Management of Cognitive Symptoms (*α* = 0.82), Management of Medical Symptoms (*α* = 0.78), and General Medical Management (*α* = 0.94) [38]. Caregivers are asked how “true” statements are regarding their (1) knowledge, (2) ability to care for, and (3) make decisions about complex care tasks, as well as their level of confidence with various tasks. Scores range from 25 to 125, with higher scores indicating higher caregiver self-efficacy levels with complex care.

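### The protocol does not fix whether there is one primary outcome or several, so 5% error control holds only if the 8-item scale alone is primary

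*Protocol article*

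**What the plan says.** The protocol article gives two accounts of what is primary.

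- **One primary measure.** Under Overall family caregiver self-efficacy: "The primary outcome measure in this trial will be the change in caregivers’ average scores on the 8-item Caregiver Self-Efficacy Scale".
- **More than one.** That sentence stands under the plural heading "Primary outcome measures". The next subsection under the same heading, Family caregiver self-efficacy with complex care, adds two scales. For the first, "the authors generated a 16-item measure structured after the Caregiver Self-Efficacy Scale" (scored 0 to 80). The second is the Caregiver Confidence in Sign/Symptom Management Scale (25 to 125), introduced with "While not measuring self-efficacy per se, the related construct of caregiver confidence with complex care will also be measured". Secondary measures begin only after these.
- **The objective.** The Primary objective asks whether the programme "improves caregiver self-efficacy (primary outcome) overall and related to complex care for persons living with AD/ADRD", and labels only depressive symptoms and appraisal of behavioural symptoms as secondary.

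The section Direct effects of the Learning Skills Together intervention sets a joint Wald test of group by time at 0.05. If that is significant, each interaction coefficient is tested at p < 0.05, and a positive coefficient supports the hypothesis. Then: "These analyses will be repeated for the outcomes measuring self-efficacy with complex care tasks, as well as secondary outcomes". No order, gate or split of alpha between scales is given, and nothing says whether success needs one scale or all.

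**The concern.** The joint test protects the time-point coefficients within one scale. Nothing protects the claim across scales. If complex-care self-efficacy is also primary, a significant result on any of two or three scales could be presented as a positive primary outcome, and the choice between readings could be made after the results are seen.

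The scales are not interchangeable. The protocol says that no validated scale exists for complex-care self-efficacy and that the authors wrote the 16-item one. Participants are not blinded. A primary claim resting on that scale alone would be weaker than one resting on the 8-item scale.

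**Working it through.** **1. The plan's own figure.** Inputs from Sample size {14}: d = 0.54, 80% power, two-sample t-test, alpha 0.05, 1:1 allocation. Two-sided testing is assumed, since the section does not say. The normal approximation, n per arm = 2(1.960 + 0.842)²/0.54², rounds up to 54, or 108 in total. The exact noncentral t gives 55 per arm, or 110, with power 80.1%. The stated N = 110 is reproduced, and it is a calculation for one outcome tested once at 0.05.

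**2. Number of scales on each reading.**

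- The sentence naming the 8-item scale governs: one.
- The Primary objective governs: at least two (8-item and 16-item).
- The plural heading governs: three. The analysis section does not name the confidence scale. Its inclusion is inferred from the plural word for the complex-care outcomes and from its scoring note, which reads higher scores as higher complex-care self-efficacy.

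**3. Chance of at least one false-positive joint test when any one scale suffices.** For k independent scales it is 1 − 0.95^k: 1 − 0.95² = 9.75% and 1 − 0.95³ = 14.3%. For correlated scales, 3-df Wald tests at 0.05 were simulated with no true effect. The protocol gives no correlation between scales, so a range is assumed.

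| Scale correlation | Two scales | Three scales |
|---|---|---|
| 0 | 9.75% | 14.3% |
| 0.5 | 9.2% | 12.7% |
| 0.8 | 8.0% | 10.2% |
| 0.9 | 7.2% | 8.6% |

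With one scale the rate is 5%. If all scales had to succeed, it would be at most 5%.

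**4. Chance of a false claim of benefit under the plan's rule.** The event is a joint test significant at 0.05 together with at least one positive coefficient at p < 0.05. It was simulated with equal correlation of 0.2 to 0.7 between the three time contrasts and 0 to 0.8 between scales, both assumed.

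| Scales | False claim of benefit |
|---|---|
| One | 1.7% to 2.4% |
| Two | 2.8% to 4.7% |
| Three | 3.6% to 7.0% |

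**5. Cost of keeping several primaries.** The same t-test calculation with Bonferroni gives:

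- two scales at 0.025 each: N = 134 for 80% power; power at N = 110 is 71.1%;
- three scales at 0.05/3 = 0.0167 each: N = 148; power at N = 110 is 65.5%.

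**The case against.** The strongest reply is that the article says in the singular which measure is primary. Mediation uses that same 8-item scale, and the sample size is for one test. On that reading the joint test holds the error at 5%. This stands. A reader might infer from the list under the primary heading that the primary error rate simply is not 5%. The documents do not support that, because no passage says that success on any one scale is enough. The sample size does not settle the matter either way, since it takes its effect from pilot self-efficacy scores without naming the scale.

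Four further points have force.

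- Inclusion of the confidence scale in the 0.05 testing is an inference, and the protocol itself says that this scale does not strictly measure self-efficacy.
- The joint-test figures count rejections in either direction. The false-benefit figures are nearer to the harm at issue, and they are smaller.
- Independence is an extreme case, since the 16-item scale was modelled on the 8-item one.
- A reader might infer that the 16 items mirror the intervention's curriculum. Only one item is printed, on incontinence. It is a topic of the intervention and not of the control programme, but the other 15 items are not shown.

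Detailed multiplicity rules may also stand in an analysis plan that is not shown, so their absence here is not the finding. The number of primary outcomes, however, is stated in this article, and stated inconsistently.

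**Conclusion.** The concern holds in conditional form: the article leaves open whether one, two or three scales are primary, and its test rule suits only one. If any one scale counts as success, joint-test error is about 7-10% for two scales and 9-14% for three. The chance of a false claim of benefit is roughly two to three times its single-scale value of about 2%, unless the scales are very highly correlated. These sizes rest on the assumed correlations and on the any-one-scale rule, which the text neither states nor excludes. The contradiction between the objective, the heading and the singular sentence rests on no assumption.

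**What to change.** State in the Primary objective, in both subsections under the primary-outcome heading, and in the direct-effects analysis section that the 8-item Caregiver Self-Efficacy Scale is the sole primary outcome. This agrees with the single-test sample size and with the mediator in the mediation analysis. Move the 16-item scale and the confidence scale to key secondary outcomes, name both in the analysis section, and test them in a stated order at 0.05 only if the primary joint test is significant.

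The change costs wording through the amendment route that the protocol already describes, and a registry update if the entry differs. N = 110 stays. The downside is that the complex-care scales carry a confirmatory claim only if the primary succeeds. If the team wants several primaries instead, it should say so and split alpha, at the cost in step 5 of the working.

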#### Self-efficacy as a mediator of intervention effects

To test self-efficacy as a mediator of secondary outcomes, we will adopt a structural equation modeling approach, which comprises two sequential models. In this analysis, the outcome will be the change score for depression or appraisal of BPSD, which is calculated by the score at 6 months minus the score at baseline. The mediator will be the change score for self-efficacy, tested using the Self-Efficacy Scale-8, calculated by 3 months minus the baseline score. Direct and indirect effects will be estimated using Baron’s and Kenny’s method [54] (Fig. 2).

**Fig. 2 Fig2:**

Mediation model to test self-efficacy as a mediator of secondary outcomes

#### Effect modification by race, ethnicity, and gender

To compare intervention effects on primary and secondary outcomes according to caregiver race, ethnicity, and gender, the investigators will first compare average change scores between study arms among African American vs. non-African American, non-white Hispanic vs. non-Hispanics, and female vs. male gender. Next, the researchers will include group × race/ethnicity/gender and group × time × race/ethnicity/gender effects in the GEE models to test effect modifications.

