**Methods:**

To test the efficacy of *LST*, we will conduct a two-arm single-site randomized controlled trial (RCT) with *N* = 200 family caregivers of persons living with AD/ADRD. Eligible family caregivers will be randomly assigned to participate in either the *LST* intervention or a structurally equivalent control condition focused on healthy living. All family caregivers will complete four surveys, including a baseline survey administered prior to randomization, a post-intervention survey, and a 3- and 6-month follow-up survey to assess change in study outcomes. Between-group comparisons of each outcome will be evaluated using generalized estimating equation models. Mediation analyses will assess family caregiver self-efficacy as the intervention’s mechanism of change in depressive symptomology and BPSD. We will also examine caregiver race, ethnicity, and gender as effect modifiers of the intervention.

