### Secondary objectives

The secondary objective of this study is to determine whether intervention effects, if found, occur equitably among caregivers according to caregiver race, ethnicity, and gender. Race/ethnicity (non-Hispanic Black, non-White Hispanic) and female gender will be tested as effect modifiers. Recent findings suggest that African American caregivers, for example, may benefit less than caregivers from other racial backgrounds in self-efficacy-focused interventions due to a potential ceiling effect [29].

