### Outcomes {12}

Outcome measures will be assessed using the average change score from baseline scores until each post-intervention survey. Follow-up data collection will occur within 3 weeks post-intervention, 3 months post-intervention, and 6 months post-intervention.

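### The effect-modification GEE lists group × modifier and group × time × modifier but not time × modifier, so as printed its three-way term measures subgroup differences in change within the LST arm only

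*Protocol article*

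**What the plan says.** The secondary objective is to "determine whether intervention effects, if found, occur equitably among caregivers according to caregiver race, ethnicity, and gender".

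The base model is set out under Direct effects of the Learning Skills Together intervention: "The models will include group assignment (intervention), time, and interaction between the group and time". The intervention is judged on the interaction: "A multivariate Wald test will be performed to see whether there is any group × time interaction". If that joint test is significant, "we will test if each regression coefficient of the group × time interaction demonstrates a" p-value below 0.05. With four surveys, the first before randomization, this implies that baseline is one of the responses.

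Under Selecting covariates, "Important covariates such as age, gender, race, and ethnicity will be included in models, regardless of their balance between two groups", which supplies the modifier main effects.

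The section Effect modification by race, ethnicity, and gender first compares average change scores between arms by subgroup, with no test or decision rule. Then "the researchers will include group × race/ethnicity/gender and group × time × race/ethnicity/gender effects in the GEE models to test effect modifications". Time × modifier appears neither there nor elsewhere in the article.

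The Outcomes section words the measure differently: "Outcome measures will be assessed using the average change score from baseline scores until each post-intervention survey".

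**The concern.** A three-way interaction isolates effect modification only if all the two-way terms beneath it are in the model. The printed list supplies group × modifier, and the base model supplies group × time. The missing term, time × modifier, is the one that lets control caregivers of different subgroups change differently over time.

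Without it, any tendency of a subgroup to change more or less whichever arm it is in has no place in the control arm's part of the model, and appears in the three-way term instead. The trial could then report unequal benefit where the LST effect is equal, or equal benefit where it is not. This is the stated secondary objective and the reason given under Trial design for oversampling two groups of caregivers. The primary comparison is not affected.

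**Working it through.** **The plan's own figure.** The article states no sample size or power for effect modification. Its only figure is N = 110 for d = 0.54, 80% power and α = 0.05. Taking the test as two-sided, the normal approximation gives 2 × (1.960 + 0.842)² / 0.54² = 53.8, so 54 per arm; the exact t calculation gives 55 per arm (power 0.801), or 110. It is reproduced and not in dispute. N = 110 (after 6 months) and N = 200 (enrolled) serve below as the range.

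**What the printed terms estimate.** Take one binary modifier, four waves (0 = baseline) and 0/1 coding. Let M(arm, t) be the mean outcome in the subgroup minus the mean in the rest, in that arm at wave t. Each arm has 8 cell means (4 waves × 2 modifier levels).

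- LST arm: group (1), group × time (3), group × modifier (1) and group × time × modifier (3) give 8 parameters of its own. It is saturated.
- Control arm: intercept (1), time (3) and modifier (1) give 5 parameters for 8 means. M(control, t) is forced to be constant over time.

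Hence, at follow-up t:

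- as printed: three-way(t) = M(LST, t) − M(LST, 0);
- with time × modifier: three-way(t) = [M(LST, t) − M(LST, 0)] − [M(control, t) − M(control, 0)].

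Only the second is effect modification.

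**Size of the bias.** Let c be a subgroup difference in change common to both arms at every follow-up, and δ the true effect modification, both in SD. As printed, the three-way coefficient equals δ + c; in the full model it equals δ.

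- δ = 0, c = 0.30: 0.30 as printed, 0 in the full model.
- δ = 0.30, c = −0.30: 0.00 as printed, 0.30 in the full model.
- δ = 0.30, c = 0: 0.30 in both.

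**Group × modifier.** As printed, this is M(LST, 0) minus the single constant fitted to the control arm. With exchangeable correlation that constant averages the four waves, three of which contain c. The coefficient is therefore −(3/4)c, or −0.225 for c = 0.30, with no baseline imbalance at all. In the full model it is the baseline contrast, and is 0 here.

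**False-positive rates.** Data were simulated with an equal LST effect in all subgroups, complete data and a robust 3-df Wald test on the three-way terms at 0.05. Assumptions not in the documents: within-person correlation 0.5, 30–40% in the subgroup (the 0.2 SD row uses 30%), and the values of c.

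| Common difference c | As printed, N = 110 to 200 | With time × modifier |
|---|---|---|
| 0 | about 8–10% | about 6–9% |
| 0.2 SD | about 16–18% | about 6–9% |
| 0.3 SD | about 23–34% | about 6–9% |
| 0.5 SD | about 47–70% | about 6–9% |

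Rates above 5% in the right-hand column and the top row reflect the robust Wald test at this sample size and simulation error, not the missing term.

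**Precision.** With equal arms, the full model subtracts an independent control-arm contrast of the same variance, so the standard error of each three-way coefficient rises by √2 = 1.41. At N = 200, 30% in the subgroup and correlation 0.5, the change score has variance 2 × (1 − 0.5) = 1. The standard error is √(1/30 + 1/70) = 0.218 as printed and √(2 × 0.0476) = 0.309 in the full model. The smaller figure belongs to a different quantity, so it is no real advantage.

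**The case against.** The strongest reply is that the sentence does not claim to list every term. It also omits the modifier main effects, which come from another section. Statisticians normally include all lower-order terms, the article is condensed, and an analysis plan may complete the model. That stands in part: the documents do not show that a non-hierarchical model will be fitted. But the sentence names one lower-order interaction and omits the other, so this is more than missing detail. Followed as printed, it answers the wrong question.

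Four stronger readings are tempting and are not supported.

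- That nothing indicates which term decides. The Direct effects section makes group × time the treatment effect, so its modification by subgroup is group × time × modifier. It should be named, but it is largely implied.
- That a significant group × modifier term is simply chance imbalance at baseline. This holds only in the full model; as printed the term also carries −0.75c. If change scores were the response, as the Outcomes section could be read, it would be modification at the first follow-up, and a constant common difference would do no harm. The emphasis on group × time in the Direct effects section points to baseline being a response.
- That the article itself predicts the damaging pattern. Secondary objectives mentions a ceiling effect as a reason why African American caregivers may benefit less from such interventions. That describes true modification, not smaller change in both arms. The Bivariate analyses section expects no significant change in controls.
- That false positives of 30–70% are to be expected. They need c of 0.3–0.5 SD. One rough anchor is the reduction from d = 0.68 to 0.54 for possible control improvement, 0.14. If 30% of controls did not improve at all, the others would improve by 0.14 / 0.7 = 0.20 SD, which gives the 16–18% row.

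The preliminary comparison of change scores between arms within subgroups does remove common change, and could expose a spurious three-way result. With no test or decision rule, it does not repair the GEE test.

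**Conclusion.** The point holds as a specification error in the printed model for the secondary objective. With the listed terms and baseline among the responses, the three-way coefficients equal true effect modification plus any subgroup difference in change common to both arms. That identity does not depend on the simulation.

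How much it matters depends on a common difference that the documents do not give. At zero there is no bias; at 0.2 SD the false-positive rate is roughly twice that of the full model; at 0.5 SD it is about half or more of trials. These rates rest on the assumed correlation, subgroup share and complete data. The wording may be shorthand, so the correction is advisable rather than critical.

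**What to change.** In the section on effect modification, state that the GEE contains group, time, the modifier and all lower-order interactions, explicitly including time × modifier, together with group × time × modifier. Name the joint Wald test of the group × time × modifier coefficients as the test of effect modification, in line with the joint test used for the intervention effect. State that baseline is one of the responses, and that group × modifier is then a lower-order term not interpreted as effect modification.

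The change needs a sentence or two, three extra parameters per binary modifier and no new data. Its price is precision: the standard error of the three-way coefficients is about 1.41 times that of the printed model, because the control arm's subgroup difference must now be estimated as well. That is the honest uncertainty for this question.
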